## Statistical Analysis Method

1. **Definition of Analysis Sets**

### Efficacy Analysis Set

Subjects who meet the inclusion/exclusion criteria, have been enrolled in this study, received the investigational product at least once, and have had their weight measured post-baseline will be included in the efficacy analysis set.

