## Rationale

This study is a large-scale, prospective, multicenter, non-interventional database observational study aimed at observing the weight loss effects, efficacy, and safety of Envlo Tab./Envlomet SR Tab. in patients with Type 2 diabetes over 24 weeks.

As a single-arm observational study, the number of subjects was calculated using G*Power 3.1.9.7, referencing the mean and standard deviation of the changes in weight and body mass index (BMI) from baseline to 12 or 24 weeks from previous Phase 2 and Phase 3 clinical studies (Figure 2) ^20)^

[Assumptions]

- Effect size: 0.25 (Mean of difference 2.5, SD of difference 10.0)
- Power: 0.95
- α error: 0.05
- Drop-out rate: 30%

[figure not shown]

Figure 2. Sample Size Calculation (G*Power)

Based on previous studies, assuming an average weight change of 2.5 kg and a standard deviation of 10.0 for the intervention with Envlo Tab. or Envlomet SR Tab., the effect size is 0.25. Setting the power: 0.95, α error: 0.05, the total required sample size is estimated to be approximately 210 subjects. Considering a drop-out rate of about 15%, we plan to recruit around 240 subjects.

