## Inclusion Criteria

Select individuals who meet all of the following criteria:

1. 1) Adults aged 19 to 80 years, both male ∙and female
2. 2) Patients with Type 2 Diabetes who, based on medical judgment by the investigator (responsible physician) and according to the approved indications, are about to receive Envlo Tab. or Envlomet SR Tab. for the first time

- Enavogliflozin monotherapy

- Enavogliflozin combination therapy with two agents (in combination with metformin)

- Enavogliflozin combination therapy with three agents (in combination with metformin and a DPP4 inhibitor)

1. 3) Patients with pre-obesity or higher stages according to the 2022 Obesity Treatment Guidelines of the Korean Endocrine Society*

* Obesity Treatment Guidelines of the Korean Endocrine Society

- Pre-obesity: BMI 23-24.9 kg/m^2^

- Stage 1 obesity: BMI 25-29.9 kg/m^2^

- Stage 2 obesity: BMI 30-34.9 kg/m^2^

- Stage 3 obesity: BMI >35 kg/m^2^

4) Individuals who plan to engage in appropriate exercise and dietary therapy for blood glucose control during the observational study period

5) Women of childbearing potential and men who agree to use appropriate contraceptive methods* or have no plans for pregnancy during the observational study period

*Hormonal contraceptives, intrauterine device (IUD) or intrauterine system (IUS) implants, vasectomy, tubal ligation, double barrier methods (simultaneous use of cervical cap or diaphragm with male condom), etc.

6) Individuals who have listened to and understood the detailed explanation of the observational study and the characteristics of the investigational products, and have voluntarily signed a written informed consent agreeing to participate in the study and to comply with subject precautions during the study period

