## Exclusion Criteria

Individuals who meet any of the following exclusion criteria will be excluded from this observational study:

1) Individuals with diabetes other than Type 2 Diabetes (e.g., Type 1 Diabetes, Diabetic Ketoacidosis, Gestational Diabetes, etc.)

2) Individuals who fall under the contraindications for administration according to the approved conditions of Envlo Tab./Envlomet SR Tab.

- Patients with hypersensitivity or a history of hypersensitivity to any component of Envlo Tab. or Envlomet SR Tab.

- Patients with an eGFR less than 30 mL/min/1.73 m²

- Patients with renal impairment with an eGFR less than 60 mL/min/1.73 m², end-stage renal disease, or those on dialysis

- Individuals with moderate to severe hepatic impairment (AST or ALT > 3 times the upper limit of normal, Total Bilirubin > 2 times the upper limit of normal, hepatitis, or liver failure)

- Individuals classified as class III or IV according to the New York Heart Association (NYHA) classification

3) Individuals who have undergone treatment with obesity medications or weight loss drugs, or other treatments (surgery, diet, etc.) leading to unstable weight within 3 months prior to the enrollment date

4) Individuals with mental incapacity

5) Pregnant or breast-feeding women

6) Individuals participating in another clinical study and receiving (applying) investigational drugs or investigational medical devices

7) Individuals deemed unsuitable for participation in this observational study based on the judgment of the investigator (responsible physician)

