## Completion and Withdrawal/Dropout of Observational Study

1. **Completion and Termination of Observational Study**

A subject is considered to have completed the observational study upon completing the close-out visit procedures at the 24-week point after their first visit (baseline) and the investigational product administration. This observational study is deemed complete when the last subject finishes their observational study participation.

1. **Withdrawal/Dropout of Observational Study**

Subjects can discontinue their participation in the study at any time at their discretion. The investigator or sponsor can also withdraw or drop a subject’s participation at any time for safety, behavioral, or administrative reasons. If a subject is withdrawn/dropped due to an AE, every effort should be made to follow the course of the AE in the subject. The following are conditions under which a subject might be withdrawn/dropped from the study, and the investigator shall enter the collected study data into the eCRF up to the point of withdrawal/dropout:

A subject may be withdrawn or dropped from the observational study if:

1. A subject not meeting the inclusion/exclusion criteria was discovered during the observational study
2. Adverse Event(AE)

: If the investigator determines that it is difficult to continue the observational study due to an adverse event

1. Withdrawal by Subject (or his/her legal representative)
2. Non-Compliance with Investigational Product

: Subjects do not agree to or follow the investigator’s instructions related to the investigational product.

1. Lost to Follow-Up

: Subjects cannot be contacted for follow-up

1. Physician Decision

If a subject is withdrawn/dropped, the investigator must notify the sponsor and make every effort to complete the end-of-observation study evaluation. The reasons for dropout will be recorded in the electronic-case report form (eCRF) and the subject’s source document. Any withdrawn subject cannot participate in the same study again.

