## Information Collected and Observation Items

### Observation Item and Method

1. **Obtaining Written Consent and Assigning Enrollment Numbers to Study Subjects**

Before collecting data related to this study, the investigator must explain the purpose and details of the study to the study subjects through an information sheet and obtain voluntary consent. This consent must include the subject's name, signature, and the signing.

The date of written consent and Visit 1 (Baseline, Day 0) may differ, but consent must be obtained before participation in the clinical study.

Enrollment numbers for subjects are automatically assigned in the eCRF upon obtaining consent. Subject numbers are 6 digits and formatted as “AXX-ZZZ”, where:

- “A”: Classification code
- “XX”: Institution number (001, 002 -)
- “ZZZ”: Subject number at each institution in the order of consent (001, 002 -)

1. **Inclusion/Exclusion Criteria Confirmation**

Inclusion/Exclusion criteria are confirmed at Visit 1 (Baseline, Day 0) to verify if all inclusion criteria are met and none of the exclusion criteria apply.

1. **Demographic Information**

At Visit 1 (Baseline, Day 0), the following information is collected to verify the subject's basic information. Pregnancy status is collected through interview or existing pregnancy test results, if available.

- Initials
- Gender
- Birth month and year, Age (in full years)
- Pregnancy and breastfeeding status

1. **Information on Type 2 Diabetes**

At Visit 1 (Baseline, Day 0), the diagnosis date of Type 2 diabetes will be collected to confirm the purpose of administering Envlo Tab. or Envlomet SR Tab.

1. **Medical History Review**

For medical history, any clinically significant medical conditions or abnormalities observed before Visit 1 (Baseline, Day 0), excluding the target disease, will be defined. The diagnosis name and date of each condition will be collected for medical history within 6 months prior to Visit 1 (Baseline, Day 0) and ongoing conditions.

1. **Alcohol/Smoking/Lifestyle Information**

At Visit 1 (Baseline, Day 0), the following information is collected to verify the subject's basic information, and any changes will be additionally collected at each subsequent visit.

1. Drinking history
   - Current Drinker^*^: ≥ 12 glasses (units) in a lifetime and drinking at least once in the last 12 months
   - Former Drinker: Has consumed at least 12 units of alcohol in their lifetime but has not drunk in the past 12 months

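### The single efficacy set requires a follow-up weight even for glycaemic endpoints, and drops weighed subjects for late-found ineligibility without tying this to Visit 1 facts or a decision blind to weight

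*Protocol*

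**What the plan says.** Protocol section 8.2, Efficacy Analysis Set, gives the only efficacy population. It admits "Subjects who meet the inclusion/exclusion criteria, have been enrolled in this study, received the investigational product at least once", and closes with the data condition: "and have had their weight measured post-baseline will be included in the efficacy analysis set". No time point is named, so one weight at either follow-up visit is enough. There is no version of the set specific to an endpoint. The Secondary Efficacy Endpoints paragraph in the same section names no other set. Section 8.1 places HbA1c change, FPG change and three HbA1c responder proportions among the secondary efficacy endpoints.

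On eligibility, section 4.4 puts the check at entry: "Inclusion/Exclusion criteria are confirmed at Visit 1 (Baseline, Day 0) to verify if all inclusion criteria are met". Section 3.5 lists among the grounds for withdrawal: "A subject not meeting the inclusion/exclusion criteria was discovered during the observational study". Some criteria rest on intention or judgement. Inclusion criterion 4 reads: "Individuals who plan to engage in appropriate exercise and dietary therapy for blood glucose control during the observational study period". Exclusion 7 is the investigator's view of suitability.

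On data collection, section 4.3 makes no visit or test compulsory, while section 4.4 plans a weight at each visit and takes laboratory values from routine care. The design has no comparator; section 3.2 begins: "As a single-arm observational study, the number of subjects was calculated using G*Power 3.1.9.7".

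**The concern.** An analysis set should not make one endpoint's data a condition for analysing another, and should not allow exclusions to be decided once the outcome is visible.

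On the first count, a missing weight says nothing about whether HbA1c was measured. Leaving such a subject out of the HbA1c analysis loses information for no reason connected with HbA1c.

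On the second, the investigator knows the treatment and sees the weight. If an eligibility failure is identified after follow-up has begun, the decision to classify it as such can be influenced by the result. With a single arm, any selective removal shifts the mean change directly, and no control group offsets it. Both the estimate and the paired test of the primary endpoint would carry that shift.

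**Working it through.** **The plan's own figure.** Section 3.2 gives mean change 2.5 kg, SD 10.0 kg (effect size 0.25), α 0.05 and power 0.95; section 8.2 makes tests two-sided. The normal approximation gives (1.960 + 1.645)² / 0.25² = 208. The exact noncentral t gives n = 210 with power 0.9501, which matches the stated figure of about 210. Neither weakness depends on this number, and the fix does not change it.

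**Part (a): weight as the condition for other endpoints.** Take an eligible, dosed subject with HbA1c at baseline and week 24 but no recorded follow-up weight.

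| Analysis | Governing text | Subject included? |
|---|---|---|
| HbA1c and FPG change (secondary efficacy) | 8.2 Efficacy Analysis Set | No |
| HbA1c responder proportions (secondary efficacy) | 8.2 Efficacy Analysis Set | No |
| Laboratory and vital-sign summaries (safety) | 8.2 Safety Analysis Set, which has no weight condition | Yes, on the natural reading |
| Lipid, liver and renal markers (exploratory) | No set named | Unclear |

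The safety summaries are only a partial substitute. They test change at week 24 only and contain no responder proportions.

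The cost in precision, if a share f of those with a result is lost, is 1/√(1 − f) − 1. The documents give no f. At f = 5% intervals widen by 1/√0.95 − 1 = 2.6%; at f = 15%, by 1/√0.85 − 1 = 8.5%. The upper value equals the whole 15% dropout allowance in section 3.2, and many dropouts would have neither value, so the true loss is likely to be well below it.

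**Part (b): removal for ineligibility found later.** Read together, section 8.2 makes eligibility a condition of membership, and section 3.5 foresees ineligibility coming to light during follow-up. Section 4.4 confirms eligibility at Visit 1 but does not make that decision final for the analysis set. No text requires the classification to be made without the weight data.

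If a share f with mean change m is removed from a population with mean −2.5 kg, the apparent loss rises by f(m + 2.5)/(1 − f). For change distributed as N(−2.5, SD²), the mean among weight gainers is −2.5 + SD·φ(2.5/SD)/[1 − Φ(2.5/SD)]:

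- SD 10 kg (the plan's value): +7.14 kg; 40.1% of subjects are gainers.
- SD 4 kg (an assumption): +2.44 kg; 26.6% are gainers.

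For example, at SD 10 and f = 5%: 0.05 × (7.14 + 2.5)/0.95 = 0.51 kg. The documents give no removal share, so f is a range:

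| Share removed (assumed) | All from gainers, SD 10 | All from gainers, SD 4 | At random from the below-average half, SD 10 | Unrelated to weight |
|---|---|---|---|---|
| 2% | 0.20 kg | 0.10 kg | 0.16 kg | 0 |
| 5% | 0.51 kg | 0.26 kg | 0.42 kg | 0 |
| 10% | 1.07 kg | 0.55 kg | 0.89 kg | 0 |

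The fourth column is f·SD·√(2/π)/(1 − f). Against the planned 2.5 kg, the gainer columns run from 8% to 43% (SD 10) and from 4% to 22% (SD 4).

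The larger entries need implausible conduct. Removing 5% or 10% of all subjects from gainers alone means declaring 5/40.1 = 12% or 10/40.1 = 25% of gainers ineligible at SD 10, and 5/26.6 = 19% or 10/26.6 = 38% at SD 4.

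**The case against.** The strongest reply to part (b) is that the protocol nowhere provides for re-judging eligibility. The check is at Visit 1. The cited criteria are anchored at entry: criterion 4 is a plan held at enrolment, which later inactivity does not falsify, and exclusion 3 looks back three months from enrolment. Section 3.5 is a list of withdrawal grounds, not an analysis-set rule, and to discover ineligibility naturally means finding a fact that already existed. Poor compliance and physician decision are separate grounds and do not remove anyone from the set. Record changes are audit-trailed. All this stands, and it rules out the stronger reading that a reader might infer, namely that the plan lets investigators drop subjects who fail to lose weight, or that the weight result is overstated. It does not close the gap: membership still turns on eligibility, late findings are foreseen, and nothing confines them to baseline facts or separates them from the weight.

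On part (a), a reader might infer that glycaemic data are thrown away. That is too strong: the raw laboratory and blood pressure values can enter the safety summaries, and weight is planned at every visit, so a laboratory result is the likelier missing item. What remains is exclusion from the efficacy analyses themselves.

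It can also be said that such rules belong in an SAP. But the protocol has already stated the definition, and an SAP that follows it inherits both weaknesses.

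**Conclusion.** The point holds in limited form. Part (a) follows directly from the text: a follow-up weight is required for efficacy endpoints that do not use weight. Its effect is probably small; even an assumed loss of 5% to 15% widens intervals by only about 3% to 8%.

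Part (b) is an opening, not a demonstrated bias. Its size depends on how many subjects are removed and why, which the documents do not tell us. It ranges from zero, if removal is unrelated to weight, to about 0.2 to 0.5 kg if 2% to 5% of subjects are removed and all are gainers at the plan's SD. That calculation also assumes normally distributed changes. The correction is worth making because the rule governs the primary result, there is no comparator, and the change costs little.

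**What to change.** Reword the Efficacy Analysis Set paragraph in section 8.2 as follows:

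- Include enrolled subjects with at least one dose, a baseline value and at least one post-baseline value of the endpoint being analysed.
- Exclude for ineligibility only on documented facts dated at or before Visit 1. These include age, diagnosis, BMI, laboratory limits and recorded prior obesity treatment under exclusion 3. That last item belongs on the list because it can be documented and bears directly on weight.
- List these exclusions before database lock, without sight of follow-up weight.
- Do not exclude on a later re-judgement of inclusion criterion 4 or exclusion 7.
- Report a sensitivity analysis of all treated subjects with data for the endpoint.

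The cost is a few sentences in the protocol, slightly different n between endpoints and one extra table. The required 210 is unaffected.

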### Safety Analysis Set

Subjects who meet the inclusion/exclusion criteria, have been enrolled in this study, received the investigational product at least once according to the approved indications, and have undergone safety evaluations will be included in the safety analysis set.

1. **Methods of Analysis**
2. **General Principles**

Continuous variables will be presented as descriptive statistics (number of subjects, mean, standard deviation, median, minimum, maximum), and categorical variables will be presented as frequencies and percentages. Unless otherwise specified, all tests will be two-sided with a significance level of 5%. All p-values will be reported to a maximum of four decimal places. If not exactly divisible, values will be rounded to two decimal places, rounding up at the third decimal place.

1. **Demographic and Baseline Characteristics**

For the demographic data (age, gender, etc.) and baseline characteristics of the study subjects, continuous variables will be presented as mean, standard deviation, median, minimum, and maximum values, while categorical variables will be presented as frequency and percentage.

1. **Efficacy Endpoints**

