- Duration of Administration (Start date, end date, ongoing status)
- Purpose of Administration
- Reason for Dose Adjustment or Discontinuation (if applicable)

1. **Laboratory Tests**

Laboratory tests are collected based on standard clinical procedures in a real-world clinical setting. If there are HbA1c results within 4 weeks prior to Visit 1 (Baseline, Day 0) or other test results collected within 3 months, these results can be used as substitutes for the laboratory tests at Visit 1 (Baseline, Day 0).

HOMA-beta is calculated using the formula [360×fasting insulin concentration (μU/mL)×fasting glucose (mg/dL)-63], and HOMA-IR is calculated with [fasting insulin concentration (μU/mL)×fasting glucose (mg/dL)/405].

Examples of Laboratory Test Items to be Collected:

| Main Laboratory Tests | HbA1c, FPG, Creatinine, eGFR, TC (Total Cholesterol), HDL, LDL, TG (Triglyceride), UACR, UGCR |
| --- | --- |
| Other Laboratory Tests  (Blood Tests) | RBC, Hemoglobin, Hematocrit, Platelet, WBC, Differential WBC count (Basophil, Eosinophil, Neutrophil, Lymphocyte, Monocyte), Na, K, Cl, P, Ca, Mg, BUN, LDH, Uric Acid, ALT, AST, ALP, γ-GTP, CPK, Total Bilirubin, Albumin, Total Protein, Glucose^*^, Insulin^*^ |
| Other Laboratory Tests  (Urinalysis) | pH, Specific Gravity, Bilirubin, Ketone, Nitrite, Protein (Albumin), RBC (Occult Blood), Urobilinogen, WBC (Leukocyte), Glucose, Creatinine |

1. **Investigational Product Administration Information**

To verify the administration details of the investigational product in this study, collect the following items at each visit:

- Medication Name (Envlo Tab. or Envlomet SR Tab.)
- Dosage and Administration (Dose per administration, unit, frequency)
- Duration of Administration (Start date, end date, ongoing status)
- Presence of Dose Adjustment or Discontinuation
- Reason for Dose Adjustment or Discontinuation (if applicable)

1. **Adverse Event**

Collect all adverse events from the start of investigational product administration until the end of the study to evaluate the safety of the investigational product and ensure the safety of the subjects.

- Occurrence of Adverse Events
- Adverse Event Information
- Name of Adverse Event
- Date of onset and resolution of Adverse Event
- Presence of Serious Adverse Event
- Presence of Unexpected Adverse Event
- Severity
- Course of Adverse Event
- Causal Relationship with the Investigational Product
- Actions Taken Related to the Investigational Product

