- Actions Taken Other than the Investigational Product
- Investigator

Adverse events occurring or ongoing at the end of Visit 3 (close-out visit at 24 weeks) will be followed up until resolution or until the investigator determines that further follow-up is no longer meaningful. For subjects who withdraw from the study before the 24-week period, adverse events will be collected up to 30 days after the withdrawal.

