### Adverse Event

For adverse events (AEs),∙adverse drug reactions (ADRs), serious adverse events (SAEs),∙serious adverse drug reactions (SADRs), unexpected adverse events∙, unexpected adverse events,∙collected during the study period, the number of subjects with events, the number of events, incidence rates, and two-sided 95% confidence intervals will be presented. The severity of the adverse events, the causal relationship with the investigational product, actions taken concerning the investigational product, other actions taken, and the outcomes of the adverse events will be summarized.

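### The Safety Analysis Set drops dosed subjects who prove ineligible or were treated off-label, so some collected adverse events fall outside the safety summaries

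*Protocol*

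**What the plan says.** The Safety Analysis Set in Protocol section 8.2 begins with "Subjects who meet the inclusion/exclusion criteria, have been enrolled in this study" and continues with "received the investigational product at least once according to the approved indications, and have undergone safety evaluations". Membership thus needs three things beyond enrolment and exposure: eligibility, on-label treatment and a safety evaluation.

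The Efficacy Analysis Set in the same section also requires eligibility. Its exposure condition is only "received the investigational product at least once, and have had their weight measured post-baseline", with no reference to the approved indications.

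Section 3.5 lists, among the reasons for withdrawing a subject, "A subject not meeting the inclusion/exclusion criteria was discovered during the observational study". The exclusion criteria in section 3.4 include "Individuals who fall under the contraindications for administration according to the approved conditions of Envlo Tab./Envlomet SR Tab", followed by hypersensitivity, renal and hepatic items and NYHA class III or IV.

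On collection, section 4.4 says "Collect all adverse events from the start of investigational product administration until the end of the study", and "For subjects who withdraw from the study before the 24-week period, adverse events will be collected up to 30 days after the withdrawal". On output, the Adverse Event paragraph of section 8.2 says "the number of subjects with events, the number of events, incidence rates, and two-sided 95% confidence intervals will be presented". It names no analysis set.

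**The concern.** A safety population is normally defined by exposure, because the question is what happened to people who took the drug. Here exposure is necessary but not sufficient. A subject who took the drug, and whose events were recorded, leaves the set if a criterion turns out not to have been met or if the use was off-label. Both conditions can be settled after dosing, so the set selects on something other than exposure.

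Safety is part of the stated objective (section 2), and section 1.2 justifies the study by the lack of effectiveness and safety data from routine practice. Routine practice includes some patients treated outside the criteria. Leaving them out narrows the safety summary to a cleaner group than the one exposed. At stake are the completeness of the case counts and, to an unknown degree, the incidence rates.

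**Working it through.** The protocol gives no figure for this point, so the check is a comparison of text followed by an illustration.

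**Text**

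1. Can a dosed subject fail the eligibility condition? Yes. Eligibility is confirmed at Visit 1 (sections 4.3 and 4.4), but section 3.5 allows for an ineligible subject being found during the study.
2. Might that subject have a contraindication? Possibly, since section 3.4 lists contraindications among the exclusions. The subject might equally have failed a criterion on BMI, age, recent weight-loss treatment or participation in another study.
3. Are that subject's events collected? Yes, from first administration, and for 30 days after an early withdrawal (section 4.4).
4. Do they enter the summaries? Not if the Safety Analysis Set is used. The Adverse Event paragraph names no set, so this is the natural reading rather than an explicit statement.
5. Is there another route into the report? The protocol states no all-treated set, sensitivity analysis or listing of events in excluded subjects.

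**Illustration**

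Inputs: N = 240 dosed (planned enrolment, section 3). Assumed, not from the protocol: k excluded subjects, ADR rate p1 in them and p0 in the rest.

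- Reported incidence (restricted set) = p0
- All-treated incidence = [(N − k)·p0 + k·p1] / N
- Share of subjects with an ADR left out = k·p1 / [(N − k)·p0 + k·p1]

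With p0 = 10%:

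| k | p1 | All-treated incidence | Share left out |
|---|---|---|---|
| 12 (5%) | 25% | (22.8 + 3.0)/240 = 10.75% | 3.0/25.8 = 11.6% |
| 24 (10%) | 25% | (21.6 + 6.0)/240 = 11.5% | 6.0/27.6 = 21.7% |
| 12 | 10% | (22.8 + 1.2)/240 = 10.0% | 1.2/24.0 = 5.0% |
| 24 | 10% | (21.6 + 2.4)/240 = 10.0% | 2.4/24.0 = 10.0% |
| 12 | 5% | (22.8 + 0.6)/240 = 9.75% | 0.6/23.4 = 2.6% |
| 24 | 5% | (21.6 + 1.2)/240 = 9.5% | 1.2/22.8 = 5.3% |

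With p0 = 5% and p1 from 10% to 30%, all-treated incidence is 5.25% to 6.25% for k = 12 and 5.5% to 7.5% for k = 24.

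For scale, the 95% half-width for a 10% rate in 240 subjects is 1.96·√(0.10 × 0.90/240) = 3.8 percentage points, larger than any shift in the table.

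**The evaluation condition**

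This condition works differently. Suppose 12 of 240 dosed subjects have no post-dose safety information and the other 228 have a 10% rate, giving 22.8 expected cases. Excluding the 12 gives 22.8/228 = 10.0%. Including them as event-free gives 22.8/240 = 9.5%. Here exclusion raises the reported rate and inclusion dilutes it.

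**The case against.** The strongest case on the other side is that the wording is restrictive but the consequence may be small or nil. Most of its points stand.

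- A reader might infer that the set removes the highest-risk patients. Only the contraindications in section 3.4 support that. Nothing in the protocol suggests more reactions in someone who is ineligible on BMI or because of participation in another study.
- A reader might infer that section 3.5 expects contraindicated patients to be found after dosing. It names no condition, does not mention dosing, and gives the discovery only as one possible reason for withdrawal.
- A reader might infer that the evaluation condition also hides reactions. The term is undefined, and a subject with a recorded event can fairly be read as having been evaluated. As shown above, that condition mainly shrinks the denominator and can raise the reported rate.
- A reader might infer that events vanish altogether. They stay in the eCRF (section 6.3), and every serious adverse event goes to the sponsor within 24 hours whatever its causality (section 6.4). The loss is confined to the summaries.
- A reader might argue that losing one serious reaction of two would halve the incidence. That presumes where the event falls, and the protocol offers no basis for it.
- The eligibility and on-label conditions overlap, because inclusion criterion 2 and exclusion criterion 2 already refer to the approved use. They should not be counted as independent losses.
- The study has one arm, its primary endpoint is weight and BMI, and no safety test or stopping rule is tied to this set.

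What does not stand is the restriction itself. The protocol fixes the definition, so it is not a detail left to an unseen SAP, and none of these points gives a reason to condition a safety population on eligibility or label compliance.

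**Conclusion.** The concern holds in a limited form. As written, the Safety Analysis Set leaves out dosed subjects later found ineligible or treated off-label. If it is used for the adverse event tables, the collected events of those subjects are missing from the summarised ADR, serious ADR and special-interest results.

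The number affected is unknown and may be zero. The direction of any bias in incidence is also unknown: upward, downward and null cases are all possible. With 5% to 10% excluded and assumed rates of 25% against 10%, incidence would be understated by 0.75 to 1.5 percentage points. With equal rates it would be unchanged, and only the case counts would be short. The protocol does not support a firm claim that the summary will look too favourable. The point should be fixed because the restriction serves no stated purpose and is cheap to remove, not because a large bias has been shown.

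**What to change.** In section 8.2, define the Safety Analysis Set as all enrolled subjects who received at least one dose of Envlo or Envlomet SR, with no condition on eligibility, label compliance or evaluation. State that the adverse event summaries use this set. Flag ineligible and off-label subjects and list their events separately. Report the number of dosed subjects with no post-dose safety information, because counting them as event-free can dilute the rate.

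The cost is a one-sentence change to the definition, plus a listing and a count. The adverse events are already collected, so no new data are needed. The downside is that reported incidence may shift slightly in either direction.
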